## Abstract

**Background/Objectives**: Pediatric acquired brain injury (ABI) often results in persistent challenges that extend beyond motor impairments, affecting quality of life (QoL), social participation, and engagement in physical activity. Given the complexity and chronicity of these outcomes, there is a pressing need for multidimensional interventions grounded in the International Classification of Functioning, Disability and Health (ICF). Sport-based exercise interventions, when developmentally adapted and tailored to individual interests, may promote intrinsic motivation, peer connection, and sustainable engagement—factors especially relevant in pediatric ABI populations, who often experience reduced physical activity and social isolation. However, standardized, replicable protocols specifically tailored to this population remain scarce. This study presents the protocol for a randomized controlled trial evaluating the effects of a 16-week sport-based intervention on QoL, social participation, physical activity engagement, and motor functioning tailored for adolescents with pediatric ABI. **Methods**: Participants will be randomly assigned to an intervention group or a control group receiving usual care. The intervention consists of one weekly 60-minute session, led by trained professionals in adapted physical activity and pediatric neurorehabilitation. It combines sport-based motor skill training, cooperative games, and group activities specifically tailored to each child’s developmental level, motor abilities, and preferences. Outcomes will be assessed at baseline and following the 16-week intervention period, focusing on QoL, participation, physical activity engagement, and motor functioning. **Discussion:** This study introduces a structured, child-centered model that bridges clinical rehabilitation and community-based sport. By integrating motor and psychosocial targets through a group sport-based intervention, it aims to enhance recovery across ICF domains. Findings may inform interdisciplinary practice and support the development of sustainable strategies to promote long-term engagement and well-being in adolescents with ABI.

## 1. Introduction

Pediatric acquired brain injury (ABI) refers to any non-congenital brain damage after birth in adolescents with typical neurodevelopment, resulting in a disruption of neural function [1,2]. It encompasses diverse etiologies, including traumatic brain injury, stroke, infections, and tumors [1,2].

ABI is a leading cause of disability among the pediatric population, producing complex, long-lasting impairments across all domains of the International Classification of Functioning, Disability and Health (ICF) [3,4,5]. These impairments negatively affect quality of life (QoL), limit participation, and impact physical well-being [6,7]. Consequently, adolescents with ABI require sustained support from families, educational systems, and healthcare services, imposing significant societal and economic burdens [8,9].

The multidimensional and chronic nature of pediatric ABI requires a comprehensive, interdisciplinary, and holistic approach that extends beyond conventional therapies focused primarily on physical recovery, to encompass psychosocial dimensions critical for global well-being [10,11,12,13].

In this context, exercise interventions grounded in sports have recently gained attention for their ability to simultaneously target multiple health domains in neurological populations [12,14,15,16,17]. It combines complex motor skills, cognitive engagement, and social interaction, providing a multifaceted stimulus that promotes neuroplasticity and functional improvements across different areas [12,14,15,16,17]. Particularly in pediatric populations, growing evidence highlights sport-based exercise as a promising approach to enhance motor recovery while also targeting emotional, cognitive, and behavioral sequelae [18,19]. Evidence suggests that sport-based exercise induces neurophysiological changes beneficial to executive function, mood regulation, and attention—all commonly affected in pediatric ABI [20].

Furthermore, participation in group-based exercise sessions tailored to each participant’s developmental stage and interests promotes peer interaction, self-esteem, and social engagement—factors especially relevant for adolescents who frequently experience isolation and reduced physical activity participation [21,22,23,24]. This approach also enhances intrinsic motivation, facilitating long-term adherence to active, socially integrated lifestyles, reinforcing gains across multiple ICF domains [22,23,24]. However, despite these potential benefits, there remains a lack of standardized and replicable sport-based protocols specifically designed for adolescents with ABI that explicitly integrate the ICF framework—particularly those linked to psychosocial well-being.

Therefore, the aim of the present study is to design and evaluate a sport-based exercise intervention tailored to the specific needs of adolescents with ABI. The program is tailored to the developmental characteristics and functional needs of this population, with the goal of promoting improvements in quality of life, social participation, motor function, and physical activity engagement.

## 2. Materials and Methods

This study was developed in accordance with the Standard Protocol Items: Recommendations for Interventional Trials (SPIRIT) guidelines [25]. It has been registered on Clinicaltrials.gov (Identifier: NCT06804486) and received ethical approval from the Regional Ethics Committee of Madrid (IRB approval no. EC 33.25).

### 2.1. Trial Design and Setting

The study protocol describes the methods for a controlled trial with two parallel groups. The trial will compare the effectiveness of a sport-based exercise program in combination with usual care (experimental group), versus usual care alone (control group) in adolescents with ABI. The study screening, intervention, and assessments will be carried out at a pediatric hospital in Madrid, Spain, called Niño Jesús Hospital.

A flowchart of the study design according to the CONSORT guidelines is shown in Figure 1.

### 2.2. Eligibility and Recruitment

The study will involve adolescents aged 11 to 17 years with a confirmed diagnosis of ABI, regardless of etiology, who are receiving care at the Pediatric ABI Unit of Hospital Niño Jesús. Participants may be either inpatients or outpatients and may include individuals using wheelchairs or other mobility aids. A non-probabilistic, convenient sampling approach will be used based on participant availability and interest. Healthcare professionals within the Pediatric ABI Unit will identify eligible participants according to the inclusion and exclusion criteria outlined in Table 1. Recruitment will be conducted over a three-month period. All eligible participants and their legal guardians will provide written informed consent after receiving detailed information about the study’s objectives and procedures.

### 2.3. Allocation and Blinding

Participants will be randomly allocated to either the intervention or control group using centralized, independent, stratified block randomization. A computer-generated random number sequence will ensure a 1:1 allocation ratio. Blinding will be maintained for assessors.

### 2.4. Interventions

#### Sport-Based Exercise and Usual Care (Experimental Group)

Participants in the experimental group will engage in a sport-based exercise program in addition to their usual hospital care sessions. The program consists of twice-weekly sessions, each lasting 60 min, over a period of three months. It is structured around a sport-based framework that integrates motor patterns and task demands from a variety of sports disciplines. Sessions are organized in a circuit format that emphasizes functional movement, progressive task complexity, and social interaction within small groups of two to four participants, grouped by age and functional capacity. Each session follows a sample structure including warm-up activities (e.g., dynamic stretching and basic motor skill drills), main circuit stations featuring sports-based tasks such as adapted ball games, obstacle navigation, and coordination drills, and a cool-down with relaxation exercises.

Session content is continuously tailored to each participant’s motor abilities to enable individualized progression, including specific adaptations such as seated or supported activities for children with limited mobility, simplified task demands for those with cognitive or behavioral challenges, and use of assistive devices as needed. Participants’ individual interests and functional goals are identified through baseline assessments and ongoing feedback, which guide activity selection and progression. All sessions are supervised to ensure accuracy and safety.

The Template for Intervention Description and Replication (TIDieR) checklist was used to ensure complete reporting of the intervention (Table 2) [26].

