### 2.8. Sample Size

The sample size estimation was based on the PedsQL, a validated outcome measure in pediatric neurological populations, including brain injury. Varni et al. (2006) reported standard deviations of approximately 10–11 points in cerebral palsy [31]. Assuming an SD of 10 points, with a two-sided alpha level of 0.05 and statistical power of 80%, the calculated sample size to detect a between-group difference is approximately 39 participants per group. Adjusting for an anticipated attrition rate of 15%, the final sample size was set at 45 participants per group.

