### 2.10. Statistical Methods

The comparability of the study groups will be assessed by the similarity of the distribution of the variables of interest at baseline. The analysis will follow standard methods for randomized controlled trials, using two-group comparisons for all participants on an intention-to-treat basis. The chi-squared test or Fisher’s exact test will be used to compare proportions. Student’s t-test will be used to compare means between groups with normally distributed data. The Mann–Whitney test will be used to compare quantitative variables between groups in the case of a non-normal distribution, as determined by the Kolmogorov–Smirnov test. Correlations between quantitative measures will be determined by Spearman’s rho correlation coefficient. Matched pair data analysis is also calculated. In addition, multivariate analysis will be performed using multiple linear regression and logistic regression, depending on the response under consideration. This will allow for adjustment of the effectiveness of the intervention for potential confounders and the identification of other variables associated with each of the outcomes. Statistical significance will be set at ≤0.05. Data will be analyzed using the Statistical Package for the Social Sciences (SPSS) software, version 27.0 (IBM Corp, Armonk, New York, NY, USA).

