## Figures and Tables

**Figure 1 jcm-14-05970-f001:**
[figure not shown]
Flowchart.

**Table 1 jcm-14-05970-t001:** Eligibility criteria.

Inclusion Criteria	Exclusion Criteria
Be aged <18 years at study entry.	Do not have a completed and signed informed consent form.
Have a medical diagnosis of acquired brain injury in the subacute or chronic stage.	Have medical comorbidities that contraindicate safe exercise (e.g., cardiac or respiratory instability, and uncontrolled seizures).
Be able to understand simple instructions from the program.	Failure to cooperate during the preliminary tests of the program.

**Table 2 jcm-14-05970-t002:** Template for intervention description and replication checklist for the intervention.

Items	Description of Items
Name of the intervention for the experimental/comparison group	Experimental group: sport-based exercise program and usual care sessions. Control group: usual care sessions.
Rationale	
Materials used in the intervention	Experimental group: The program is centered around different sports disciplines, which are adapted to participants’ functional condition, as well as different generic equipment, such as balls, chairs, tables, and platforms, among others.
Intervention procedures	Experimental group: The content of this program is designed around a sport-based framework incorporating motor patterns and task demands from various sports disciplines. It uses a circuit format to promote functional movement, progressive task complexity, and social interaction in small groups tailored by age and functional ability. Group composition will consider motor proficiency, cognitive, and behavioral profiles to balance skill levels and promote peer support. Strategies such as individualized task modification, use of visual and verbal cues, and structured routines will support engagement. Control group: Usual care encompasses a range of therapies (e.g., occupational therapy, physiotherapy, psychological support) provided by the rehabilitation services within the center. Typical frequency is 2–3 sessions per week, mainly individual or small group-based, and does not routinely include sport-based or structured group exercise. Following the post-intervention assessment, participants from this control group can participate in the same program sessions upon request.

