Provider	Experimental group: The program will be delivered by a professional with expertise in neurological disorders and adapted physical exercise. Control group: Usual care for this group will be provided by professionals from the rehabilitation center.
Mode of intervention delivery	Experimental group: Presential, group-based sessions (from two to four participants). Control group: Presential, individual sessions.
Setting of intervention	Screening, interventions, and assessments will be conducted at the pediatric hospital, located in Madrid, Spain.
Dosage	Experimental group: Participants from this group will receive a 3-month exercise program which consists of sixteen sessions, 1 h session/day for 2 days/week. Control group: This group will continue with their usual care as usual 2 days/week, over 3 months, and then will be reassessed.
Tailoring	The session’s content will be continuously tailored and adapted by a research team to meet the individual needs and functional levels of each participant, thereby ensuring precise execution and security.
Modifications	Not applicable.
Fidelity assessment	The team responsible for delivering and managing the intervention will conduct a phone follow-up every 2 weeks, as well as other strategies to monitor the adherence and quality of the intervention (session attendance, fidelity checklists). Additionally, this professional will track the progress of participants from the control group during these follow-up calls.

**Table 3 jcm-14-05970-t003:** Schedule of enrolment, interventions, and assessments from the SPIRIT guidelines.

	Study Period		
	Allocation	Baseline	Completion
*ENROLLMENT:*			
Eligibility screen			
Informed Consent			
*INTERVENTIONS:*			
Sports-based exercise + Usual Care			
Usual care			
*ASSESSMENTS:*			
Sociodemographic, anthropometric, and comorbidity data			
Health-related quality of life (PedsQL)			
Physical Activity (GPAQ)			
Participation (CASP)			
Motor functioning (BOT-2)			

Abbreviations: PedsQL, Pediatric Quality of Life Inventory; CASP, Child and Adolescent Scale of Participation; GPAQ, Global Physical Activity Questionnaire; BOT-2, Bruininks–Oseretsky Test of Motor Proficiency.

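### The experimental arm trains in small groups, but the sample size and the named tests treat participants as independent; a positive within-group correlation would make p-values too small and power lower than stated

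*Protocol article*

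**What the plan says.** **Randomisation.** Section 2.3 allocates participants individually: "A computer-generated random number sequence will ensure a 1:1 allocation ratio".

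**Delivery, experimental arm.** Section 2.4 describes a circuit programme with "social interaction within small groups of two to four participants, grouped by age and functional capacity". Table 2 (Intervention procedures) adds: "Group composition will consider motor proficiency, cognitive, and behavioral profiles to balance skill levels and promote peer support". The Discussion credits the group setting with motivation, interaction among peers and emotional regulation.

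**Delivery, control arm.** There are two statements. Table 2 (Mode of intervention delivery) sets the arms against each other: "Presential, group-based sessions (from two to four participants). Control group: Presential, individual sessions". Table 2 (Intervention procedures) says of usual care: "Typical frequency is 2–3 sessions per week, mainly individual or small group-based".

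**Sample size.** Section 2.8 uses SD 10, two-sided alpha 0.05 and 80% power, and states that "the calculated sample size to detect a between-group difference is approximately 39 participants per group". After 15% attrition the target is 45 per group. No between-group difference, ICC, group size or design effect is given.

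**Analysis.** Section 2.10 plans an analysis "using two-group comparisons for all participants on an intention-to-treat basis": Student's t-test or Mann–Whitney for quantitative outcomes, chi-squared or Fisher for proportions, and multiple linear or logistic regression for adjustment. No random effect, cluster-robust standard error or term for exercise group is named.

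**The concern.** This is an individually randomised, group-treated design. With 45 in the experimental arm there would be about 12 groups if all had four members (45/4 = 11.25) and about 23 if all had two (45/2 = 22.5). Group-mates share the sessions and one another's company, and the protocol expects that company to affect quality of life and participation, which are among its outcomes. On its own reasoning, then, outcomes within a group may be correlated.

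The named tests in their standard form assume independent observations. A positive correlation in the experimental arm enlarges the true variance of the treatment difference, but the tests do not see it. The nominal 5% test then rejects too often under the null, and a test held at the correct level has less power than Section 2.8 claims. If membership is not recorded while sessions are being delivered, a later analysis plan cannot repair this.

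**Working it through.** **Inputs from the protocol:** group size m = 2 to 4 (Section 2.4, Table 2); SD 10, alpha 0.05 two-sided, power 80%, 39 per group, 15% attrition, 45 per group (Section 2.8).

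**Assumed, not in the protocol:** ICC 0.05, 0.10 and 0.20; stable groups; clustering in the experimental arm only; the same total variance in both arms.

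**Step 1: the stated 39.** It cannot be reproduced directly because no difference is given. Solving backwards with no design effect:

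- Normal approximation: difference = 10 × (1.960 + 0.842) × √(2/39) = 6.34 points.
- Noncentral t: 6.43 points.

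At SD 10, round differences do not give 39 (6 points gives 44 per group, 6.5 gives 38, 7 gives 33). The figure of about 6.4 is therefore an inference. For attrition, 39 × 1.15 = 44.85, which rounds to 45, while 39/0.85 gives 46; this small difference is not the issue here.

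**Step 2: allow for training groups.**

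- Design effect in the experimental arm: DE = 1 + (m − 1) × ICC.
- Variance inflation of the difference: V = (DE + 1)/2.
- True type I error of the unadjusted test: 2 × [1 − Φ(1.96/√V)].
- Power of a test at the correct level, 39 per arm: Φ(6.34/(10 × √((DE + 1)/39)) − 1.96).

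Example, m = 4 and ICC 0.20: DE = 1.6, V = 1.3, √V = 1.14, type I error 8.6%, power 69%.

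| ICC (assumed) | m | V | Type I error | Power, 39 per arm |
|---|---|---|---|---|
| 0 | any | 1.000 | 5.0% | 80% |
| 0.05 | 2 | 1.025 | 5.3% | 79% |
| 0.05 | 3 | 1.050 | 5.6% | 78% |
| 0.05 | 4 | 1.075 | 5.9% | 77% |
| 0.10 | 2 | 1.050 | 5.6% | 78% |
| 0.10 | 3 | 1.100 | 6.2% | 76% |
| 0.10 | 4 | 1.150 | 6.8% | 74% |
| 0.20 | 2 | 1.100 | 6.2% | 76% |
| 0.20 | 3 | 1.200 | 7.4% | 72–73% |
| 0.20 | 4 | 1.300 | 8.6% | 69% |

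Over this range the standard error is understated by about 1–14% relative to the unadjusted one. Simulating the t-test (40,000 trials per setting, 39 per arm) gave type I errors of 5.3–8.7%, in agreement with the table.

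**Step 3: is forming groups by age and function enough to cause this?** No. Sorting experimental participants into groups on a baseline trait, with no shared effect of the sessions, left the type I error of the t-test at 5.1% (20,000 trials). The inflation comes from what group-mates share after randomisation, not from who is placed with whom.

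**The case against.** The strongest case on the other side has five parts.

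- **Group stability.** A reader might infer that the groups are fixed for the programme. The protocol does not say so, and it recruits inpatients and outpatients over three months according to availability (Section 2.2), so regrouping is possible. Rotation would weaken the clustering and call for a multiple-membership model. This stands.
- **No ICC.** A reader might also infer that the p-values are bound to be wrong, or that similar profiles within groups make them so. Neither follows. The harm needs a positive correlation induced by shared sessions, and Step 3 shows that composition alone does no damage. Nor does Section 2.10 promise confidence intervals, so none in the plan can be called too narrow. All of this stands.
- **Control arm.** Treating every control as a cluster of one relies on one of two conflicting statements in Table 2. This stands. Clustering among controls would add to the variance, not remove it.
- **The remedy can over-correct.** In a check with 39 per arm and groups of three, with no shared session effect, an unadjusted group-level analysis rejected in only 2.7% of null trials when the sorting trait correlated 0.5 with the outcome, and 1.4% at 0.7. With neither sorting nor a group effect, the between-group variance estimate was zero in 53% of runs. This is a reason to adjust for the grouping variables.
- **Scope.** Random-effects detail is commonly left to an analysis plan. That is true of the detail, but this article commits to specific tests and a specific number, and its own delivery format undermines the assumption behind both.

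**Conclusion.** The point holds in conditional form. The plan uses independence-based tests and an independence-based sample size for an arm treated in groups, where interaction within the group is an intended mechanism. If shared sessions produce an ICC of 0.05–0.20 in groups of two to four, the true type I error is about 5.3–8.6%. A correctly sized test with 39 per arm then has about 79–69% power for the back-solved difference of about 6.4 points.

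The effect is modest at ICC 0.05 and becomes material from about 0.10 upwards; the worst figures need both the largest groups and the highest assumed ICC. The size rests on an assumed ICC, on stable groups and on clustering in one arm only. At ICC 0 the planned analysis is valid as it stands.

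**What to change.** 1. Record which exercise group each participant attended at each session, and state whether membership is stable.
2. Reconcile the two descriptions of control delivery in Table 2, since they decide whether controls can be treated as unclustered.
3. Use a partially nested linear mixed model for the quantitative outcomes: a random group effect in the experimental arm, small-sample degrees of freedom such as Satterthwaite, and adjustment for baseline score, the stratification factors and the variables used to form groups. Use a multiple-membership form if groups rotate. Make this the main analysis, or at least a prespecified sensitivity analysis.
4. State the between-group difference behind the 39, and restate power for 45 enrolled per arm (45 × 0.85 ≈ 38 analysed) over a range of assumed ICCs, such as 0.05 to 0.20. This asks for an honest power statement, not for more participants.

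The cost is one data field and a different model. The downsides are somewhat wider intervals, fewer degrees of freedom with only about 12 to 23 groups, and possible conservatism if the grouping variables are left out of the model.
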